### Randomisation

When, as in our study, specific prognostic factors may influence outcomes, the best way to ensure a balanced distribution of participants across groups is to use an allocation by a minimisation process [30]. Accordingly, participants are stratified to one of the three study groups according to on their age and the severity of their tinnitus [31]. Age is included as a prognostic factor. This is based on the assumption that neurofeedback utilises the brain’s ability to reorganise itself functionally and/or structurally [32, 33]. With the current knowledge, evidence favours the hypothesis that younger individuals have greater neuroplastic potential [34] compared to older individuals. This is partially because of the association between increasing age and functional and structural brain deterioration [35, 36]. However, it would be false to believe that this deterioration affects all individuals to the same degree. With increased age comes large individual differences in brain health [34]. These differences are already apparent by the time people reach their mid-fifties [35]. Taken together, these observations have led to the following stratification categories for age in the present study: 1) ≤ 55 years; 2) > 55 ≤ 64; 3) > 64 ≤ 69; and 4) > 69. Given the conservative inclusion criterion on the primary outcome variable (18 ≥ THI score pre-intervention ≤100), stratifying participants into sub-groups based on the tinnitus distress classification by McCombe and Baguley [31] is considered a sensible option. This ensures a balanced distribution of the range of THI scores across the three groups. Importantly, this reduces the risk of heterogeneity of variance affecting the between-group outcome analysis. Thus, participants are stratified to one of four levels of tinnitus distress: 1) mild (THI 18–36); 2) moderate (THI 38–56); 3) severe (THI 58–76); and 4) catastrophic (THI 78–100).

Allocating participants to one of the three groups is performed by a researcher independent of the study. This individual, trained in the minimisation programme Minim [37], will subsequently inform the research team about the group allocation of each participant. A group allocation list is kept in a separate and password secured Excel file on the local drive of the independent researcher’s PC.

To ensure blinding of neurofeedback trial participants, two identical neurofeedback training protocols were developed. First, information about the course of the training is kept identical for participants in both groups. Second, the position of the training electrodes is the same; that is, positions FC1, FC2, F3 and F4 of the 10/10 International system were used in the training sessions. Third, the duration and intensity of the training sessions are identical for both groups; that is, all participants undergo ten sessions, each initially consisting of four but progressing to five training blocks per session. Fourth, the neurofeedback training stimulus used, i.e., a fish swimming vertically across the screen, is the same for both groups. In other words, all variables are kept constant except for the trained frequency bands, which is information not accessible to participants.

### Interventions

#### Neurofeedback training groups

The neurofeedback training sessions are designed identically for the ADR and the BTR sessions. Both training sessions will be applied unidirectionally, with the aim of a) decreasing the ADR by an increase of alpha [8–12 Hz) and/or a reduction of delta (2–4 Hz) and b) decreasing the BTR by inhibiting theta (4–8 Hz) and/or reinforcing beta (13–20 Hz) activity bilaterally over the fronto-central cortex (FC1, FC2, F3 and F4).

During each neurofeedback (NF) training session, EEG and electromyography (EMG), as well as a vertical and horizontal electrooculogram (EOG), are recorded with Ag/AgCl-sintered ring electrodes with impedances kept below 5 kΩ using a 13-channel DC-amplifier (THERA PRAX®MOBILE, Neurocare GmbH, Ilmenau, Germany; > 10 Gohm input impedance) and a sampling rate of 256 Hz. EEG electrodes are placed at F3, F4, FC1 and FC2 in accordance with the 10/10 electrode placement system [38] using an elastic electrode cap (EasyCap, Woerthsee-Etterschlag, Germany). Reference and ground electrodes are attached to the right and left mastoid, respectively. The electrode montage is identical to previous neurofeedback studies in tinnitus [14, 39] to guarantee comparability with former research. EMG is recorded with two electrodes placed at the upper descending part of the M. trapezius. To reduce artefacts produced by eye movements, a real-time EOG is recorded simultaneously using four electrodes (two electrodes at external canthi, and two electrodes at infra- and supraorbital sides). Eye movements are removed from the feedback signal during the training using an online ocular correction as described by Schlegelmilch and Markert [40]. In addition, all signals acquired during neurofeedback training are stored as raw signals for later offline processing without any calibration or filtering.

Online-processing in real time comprises a 50 Hz notch filter applied to EEG signals before direct feedback. Depending on the respective training group, BTR [theta(μV^2^/Hz)-beta(μV^2^/Hz)/theta(μV^2^/Hz) + beta(μV^2^/Hz)] or ADR [delta(μV^2^/Hz)-alpha(μV^2^/Hz)/delta(μV^2^/Hz) + alpha(μV^2^/Hz)] are extracted with a short-time-Fourier transformed moving average across the four training electrodes and fed back to participants’ monitors, using a graphical object (i.e., fish): horizontal movements of the object from left to right at a constant speed represents the temporal proceeding of the trial (i.e., sampling rate), while vertical movements of the object indicates the targeted changes in the feedback parameter (ADR or BTR), either by moving up (targeted change) or down (non-targeted change). A successful change in cortical activity (i.e., keeping the ADR or BTR above the training threshold for at least 250 ms) is rewarded with the symbol of a sun after each trial, as the only performance-dependent reinforcement. The neurofeedback training protocols are largely in line with the successful tau-(8–12 Hz; identical to our alpha frequency band)-to-delta-ratio protocol used previously [13]. It comprises 10 sessions (four runs and 10 trials; net training approximately 30 min) over the course of 4 weeks. One trial consists of 30 s of active neurofeedback training, followed by a 10-s inter trial interval, in which the last 2 s are used to determine the current baseline for both trainings. Therefore, each trial during training is individually baseline-corrected, and the feedback object always starts moving from the same position on the monitor (please see https://youtu.be/0ZD_mUFixHs for an illustration of the individual trial run). The scale of the feedback monitor is set to 2 μV. For the first training trial in the first session, the training threshold is set to 20%, corresponding to reward reinforcement when the ADR or BTR is greater than 0.2 μV for at least 250 ms. If a reinforcement rate of at least 70% is reached for a training block, the threshold is increased by 3%. In blocks with success in less than 30% of the trials, the threshold will be lowered by 2%. The following training session is started with the thresholds of the last block of the preceding session. To enhance transfer effects, we also gradually included more transfer trials in an additional block at the end of each session, starting from session 6 onwards (see Fig. 2). During transfer runs, patients will not receive any continuous feedback, but will receive reinforcement for successful trials (reward symbol; please see https://youtu.be/shcR8Ilq3mo for an example of a transfer trial). The percentage of transfer trials gradually increases with each session (20%, 40%, 60%, 80% and, finally, 100% transfer trials within the final block of a session). The transfer block is implemented to facilitate the transfer of acquired changes into daily life when no feedback of physiological signals can be provided. Transfer trials, the use of which is reviewed comprehensively in [18], have successfully been employed in other frequency-based NF-protocols [41]. To further facilitate transfer, participants are instructed to retrieve their neurofeedback experiences by designing personalised cues (i.e., printed graphics representing the mental strategy used during the neurofeedback training) and to use those cues both during within-session transfer trials and during daily life. After each session, compliance is verified by questioning the participants to identify whether they have used the transfer cards over the intervention period.

**Fig. 2 Fig2:**
[figure not shown]
Study flow divided into sessions, training blocks and trials

Before participating in the first training block in the first session, the participant is shown the training sequence on the monitor. On the trainee monitor, the fish swims horizontally from left to right on the screen in a sequence lasting 30 s. This is followed by a 10 s pause before the process is repeated. During this presentation, the therapist tells the participants that their task is to try to move the fish above the black reference line in the middle of the screen. No further instructions on how to accomplish this is given. This mirrors the instructions given in [13], thus ensuring greater comparability between results. In addition to providing these instructions, during the breaks between training blocks, the therapist briefly discusses the types of mental activities the participants developed and employed to achieve the training goals.

### Diary control group

In the diary control group, Group 3, an eight-item diary is completed each evening for 7 consecutive days, in week one and week three of the 4-week intervention period. The items are purposefully designed to make participants reflect more positively about their experience with tinnitus (e.g., ‘The tinnitus didn’t disturb me today’). As adherence to diary completion is a concern, participants have two supportive face-to-face meetings. In these, participants are informed about the content and structure of the diary and instructed on its completion. In addition, psychoeducation on tinnitus aetiology, the content of which is based mainly on recognised self-help sources [29, 42], is provided. In addition, two follow-up telephone calls are held throughout the 4-week period. The follow-up telephone calls are supportive in nature and give participants an opportunity to share their experience with the diary exercise.

#### Adherence to the interventions

To maximise treatment adherence in clinical trials in general, several suggestions have been proposed (e.g., [43–45]). Of these, three in particular are relevant to our study. First, participants will find it relatively easy to complete the questionnaires in the study because all primary and secondary outcome measures are collected via an easy-to-navigate online platform. For people without access to the internet, pen and paper versions of the questionnaires can be collected at the department or obtained via mail upon specific request. Second, for participants in both the neurofeedback and diary control groups, frequent contact with members of the research team occurs throughout the intervention period. Third, participants in the diary control group are given an incentive—a self-help book [29]—upon completion of all outcome measures.

#### Measures

##### Primary outcome measures

There are two primary outcome measures in the study. First, the change in tinnitus distress following neurofeedback training is measured with the THI [24]. The THI is a 25-item self-report instrument. Each item is rated on a three-point Likert scale with responses of ‘Yes’ = 4 points, ‘Sometimes’ = 2 points, and ‘No’ = 0 points, thus yielding a total score between 0 and 100. The instrument has three subscales, assessing functional, emotional and catastrophic reactions to tinnitus. The overall test-retest reliability of the scale is 0.92 [46]. It has been translated and validated into a German version [47, 48], which is used in the present study.

To assess the efficacy of neurofeedback training in reducing the perceived intensity, i.e., the sound perception of tinnitus, the TMI is used [49]. This is a three-item measure designed to assess the individual perception of tinnitus sound intensity, without overlapping significantly with cognitive, behavioural or emotional reactions to tinnitus. The internal consistency of the scale is excellent, with Cronbach’s α = 0.86; it also has satisfactory discriminant validity (correlation of *r* = .62 with the THI). One obstacle in the development of the TMI, noted by Schmidt and Kerns [49], is the differential scaling of its three items. This has, according to the authors, the potential to increase measurement error. Schmidt and Kerns [49] suggested converting the three items into a standardised scale. Consequently, in the present study, the response scales for all three items are standardised to a range from 0 to 100.

##### Secondary outcome measures

The German version of the Tinnitus Functional Index (TFI) [50, 51] is used in the present study to detect the responsiveness to the intervention. It assesses treatment-related changes in different areas of functionality, e.g. sleep or sense of control. It consists of 25 items, with 23 responses being rated on a Likert scale from 0 to 10, and two items, from 0 to 100. For scoring the TFI, the two items ranging from 0 to 100 are divided by 10, thus yielding a total TFI score of the 25 items between 0 and 100. Eight subscales are associated with the TFI (intrusiveness, sense of control, cognitive interference, sleep, auditory difficulties, relaxation, quality of life and emotional distress). Overall, the TFI has good test-retest reliability (0.78) and convergent (*r* = 0.86 with the THI) and discriminant validity (*r* = 0.56 with Beck Depression Inventory Primary Care) [50].

To assess changes in sleep quality following neurofeedback training, the *Insomnia Severity Index* (ISI) [52] is used. The ISI consists of seven items, with Likert responses ranging from 0 to 4. Thus, a person can score between 0 and 28 on the total scale, with higher values indicating greater sleep disturbances. The ISI has good internal consistency (Cronbach’s α = 0.91, [52]) and convergent validity (r = 0.80 with the Pittsburg Quality Sleep Index, [53]).

Changes in depressive symptoms following neurofeedback are assessed with the Personal Health Questionnaire-9 (PHQ-9 [54];), a nine-item self-report instrument with Likert scale responses ranging from 0 to 3. The total score of the scale thus ranges from 0 to 27. The internal consistency of the PHQ-9 is good (Cronbach’s α = 0.89) and a test-retest reliability of *r* = 0.84 has been demonstrated [55]. Moreover, the PHQ-9 has strong convergent validity with other scores of depression (e.g., the Beck Depression Inventory, *r* = 0.73) and the General Health Questionnaire-12 (*r* = 0.59) [56].

Further secondary exploratory research questions of the current trial focus on the moderating role of pre-treatment expectancy, perceived treatment credibility and somatic self-efficacy on treatment outcome. These moderator analyses are assessed with the following instruments: an adapted form of the treatment credibility and expectancy questionnaire [57], a German version of the somatic self-efficacy questionnaire [58], and an expectancy questionnaire developed specifically for this study.

##### Training outcomes

To keep track of individual learning curves during training, we will analyse the ADR and BTR for each participant within and across sessions. However, session 1 will be discarded because it is assumed that participants will have to habituate to the setting. On the one hand, monitoring and encouraging learning will be performed by the trainers. On a patient monitor, the trainer can keep track of training progression as the percentage decrease in the BTR or ADR compared to the individual baseline for each training block.

On the other hand, the total number of successful trials per training block is used to guide either the upwards or downward adjustment of the training thresholds. Dependent measures include the mean training level over the training blocks within a session (%), the best run of each session (maximum training level) and the total number of obtained rewards per session. Furthermore, electrophysiological training raw data gathered with the THERA PRAX® MOBILE described previously will be analysed offline with Brain Vision Analyzer v2.0 (Brain Products GmbH, Gilching, Germany).

*Preprocessing:* Data are first band-pass filtered with Butterworth zero-phase filters between 0.1 Hz and 80 Hz with slopes of 24 dB/octave at the low and 48 dB/octave at the high cut-offs. To eliminate possible line noise, the data are further refined using a band-rejection filter with a central frequency of 50 Hz, a bandwidth of 1 Hz, and a slope of 24 dB/octave. For ocular correction, we will use Gratton and Coles’ [59] algorithm, as implemented in Brain Vision Analyzer software. Using a semi-automatic raw data inspection procedure, the recorded data from the training blocks will be screened for artifacts. Planned criteria for artifact screening will be as follows: maximal voltage step of 50 μV/ms, maximal amplitude of ±100 μV, maximum allowed difference of 150 μV in each segment, values greater than 200 μV per 200 ms interval and activity below 0.5 μV in a 50-ms period as the criteria. A total of 100 ms of data will be removed before and after any detected artifacts. A thorough visual inspection will be performed to remove any possible remaining artifacts (i.e., muscle movements and short drifts or jumps over single or multiple electrodes) from the signal.

*EEG analysis:* The artifact-free training data will be segmented into non-overlapping 2-s epochs and submitted to a fast Fourier transformation (FFT) with a 10% Hamming window. The resulting data are averaged in the frequency domains (delta 2–4 Hz; theta 4–8 Hz; alpha 8–12 Hz and beta 13–20 Hz) for feedback versus transfer trials for each individual session and each individual patient across the four training electrodes. Absolute power values (μV2) for each frequency band (i.e., delta, theta, alpha and beta), theta/beta and delta/alpha power ratios, and relative power (%) are calculated.

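### The raw reward total per session is a poor learning measure: it steps up when a block is added at session 6, and the adaptive threshold flattens it; the best run is affected only slightly

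*Protocol article*

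**What the plan says.** The Training outcomes section states the purpose: "To keep track of individual learning curves during training, we will analyse the ADR and BTR for each participant within and across sessions". Session 1 is to be discarded as habituation. The dependent measures are the mean training level over the blocks of a session, and "the best run of each session (maximum training level) and the total number of obtained rewards per session".

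The length of a session is not constant. The blinding paragraph under Randomisation describes sessions as "each initially consisting of four but progressing to five training blocks per session". The section on the neurofeedback training groups gives the basic layout, "It comprises 10 sessions (four runs and 10 trials; net training approximately 30 min) over the course of 4 weeks", and then the addition: "we also gradually included more transfer trials in an additional block at the end of each session, starting from session 6 onwards". The share of transfer trials in that final block climbs from 20% to 100%. Transfer trials run without continuous feedback, but a successful one still earns the reward symbol.

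The criterion for a reward is not constant either. It starts at 20%. "If a reinforcement rate of at least 70% is reached for a training block, the threshold is increased by 3" per cent; after a block with success in under 30% of trials it falls by 2%. Each session starts at the threshold of the previous session's last block.

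The EEG analysis paragraph separately plans offline band power and power ratios, averaged for feedback and transfer trials apart, per session and patient.

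**The concern.** A learning curve needs a measure with the same meaning in every session. A raw count of rewards fails this in two ways. The number of opportunities to earn a reward rises at session 6, and the criterion for earning one moves with past performance. The first can create an apparent gain where nothing was learned. The second can hide a gain that did occur. The maximum over blocks has a weaker form of the first problem, since a maximum over five draws is on average higher than over four.

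At stake is the reading of whether participants learned to regulate the trained ratio. This bears on the trial's question of specific versus non-specific effects, and on any correlation between learning and outcome that uses these two measures. Listing several learning measures side by side, one of which jumps by design, also invites contradictory or selective reading.

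**Working it through.** **Inputs from the protocol.** Four runs, read as 10 trials each; one added block in sessions 6 to 10; trials as described in "One trial consists of 30 s of active neurofeedback training, followed by a 10-s inter trial interval"; threshold start 20%, +3% at 70% success or more, −2% below 30%, carried over. **Assumptions.** The number of trials in the added block (10 or 5; the transfer shares of 20% to 100% fit both) and, for the simulation, the trial-to-trial SD (15 or 30 points) and the initial success rate (0.2, 0.5 or 0.8).

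**1. The plan's own figure.** Each trial takes 30 + 10 = 40 s.
- Four blocks: 40 × 40 s = 26.7 min.
- Five blocks, the fifth with 10 trials: 50 × 40 s = 33.3 min.
- Five blocks, the fifth with 5 trials: 45 × 40 s = 30.0 min.

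All are compatible with the stated 30 minutes or so. The layout is reproduced, but the duration does not settle the length of the fifth block.

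**2. Step from the added block.** Opportunities go from 40 to 50 (50/40 = 1.25) or from 40 to 45 (45/40 = 1.125). At a constant 50% success rate, rewards go from 20 to 25, or to 22.5. Discarding session 1 does not help. A straight line through sessions 2 to 10 (four values of 20, five of 25) has slope 5 × (0+1+2+3+4)/60 = 0.83 rewards per session, with no learning.

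**3. Pull from the threshold.** At 50% success, P(at least 7 of 10) = 0.172 and P(fewer than 3 of 10) = 0.055, so the threshold drifts up by chance. The rule was simulated for 10,000 non-learners (trial SD 15, steps read as points). Rewards in the first four blocks:

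| Initial success rate | Session 1 | Session 10 |
|---|---|---|
| 0.2 | 9.5 | 17.2 |
| 0.5 | 19.4 | 17.2 |
| 0.8 | 28.9 | 17.2 |

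With the steps read as relative percentages the direction is the same but slower: 8.3 to 13.3, 19.9 to 18.0 and 31.4 to 19.4.

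**4. Both effects together.** Initial success 0.5, SD 15, no learning, 10 trials in the fifth block: the session total goes from 17.4 (session 5) to 21.6 (session 6). Limited to the first four blocks it goes from 17.4 to 17.3. The mean level stays at 20.0 throughout.

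**5. Masking of true learning.** Four blocks throughout, with a gain of 3 points per session: the mean level rises from 20 to 47, while rewards move only from 19.4 to 21.9 and are nearly flat (21.4 to 21.9) from session 3.

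**6. Best run.** The expected maximum of independent standard normal block means is 1.029 for four and 1.163 for five, a difference of 0.134 block-SD. With trial SD 15 a block mean has SD 15/√10 = 4.74, so the shift is about 0.6 points (simulated 24.9 to 25.5). With SD 30 it is 29.8 to 31.0. This assumes that the fifth block performs like the others. If transfer trials run 0.1 lower with trial SD 0.25 (assumed), the shift is 0.09 block-SD at session 6 and 0.01 at session 10.

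**7. If training level meant the threshold.** The best run would then move without learning from 20.0 to 11.0, 21.3 to 23.6 or 26.9 to 36.3 (initial success 0.2, 0.5, 0.8; SD 15).

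**The case against.** The strongest reply is that sound measures are already planned. The article commits to analysing the ratios within and across sessions, lists a mean training level, and derives offline power with feedback and transfer trials kept apart. The reward count and best run supplement these, and their modelling may be left to an analysis plan. This stands, and it limits the weight of the point. It does not remove it, because the article itself names a session total and a session maximum, neither tied to a number of trials or a threshold.

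The count also keeps some information. In the four-block simulation, session-10 rewards are 17.2, 19.6, 21.9 and 25.8 for gains of 0, 1.5, 3 and 6 points per session from the same starting success rate. It can therefore rank participants by rate of learning even while it is nearly flat over time.

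A reader might go further in three ways that the documents do not support.
- **That the secondary question on power changes in the trained bands would show a false step at session 6.** The offline EEG analysis fits that question, and it uses neither rewards nor thresholds.
- **That the added block biases the alpha/delta versus beta/theta comparison.** Both arms have the same block schedule, so the step is common to them.
- **That the threshold moves both measures.** Training progression is described as percentage decrease from the individual baseline, which does not involve the threshold. The best run is exposed to the threshold only if training level means the threshold, and the term is not expressly defined for the outcome.

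On the other side, the Discussion rejects automatic moment-by-moment thresholds because lowering them keeps rewards coming as performance falls. The block-wise rule is slower, but it too lowers the criterion after poor blocks, so the same reasoning speaks against reading the reward count alone as learning.

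**Conclusion.** The concern holds for the reward total and only weakly for the best run. Followed as written, the total steps up at session 6 with no learning, by 25% with 10 trials in the added block and by 12.5% with 5, at an unchanged success rate. Separately, the adaptive threshold draws the total to mid-range, so it understates learning over time. The size of that pull depends on the assumed SD, starting success rate and reading of the percentage steps; its direction was the same under both readings of the steps.

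The best run shifts by about 0.13 block-SD in expectation if the fifth block performs like the others, and by less if transfer trials go worse.

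The damage is limited to within-participant learning curves, and correlations built on them, that use these two measures. THI, TMI, the offline EEG power analysis and, as regards block count, the contrast between the neurofeedback arms are not affected. It is a modest defect in stated training measures that is cheap to correct.

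**What to change.** - Make the planned baseline-corrected ratio (mean training level), averaged over the first four feedback blocks of each session, the lead learning measure. Define training level expressly as change from the individual baseline.
- Report rewards as a rate per feedback trial in blocks 1 to 4, always with the threshold in force, and not as a raw session total. Restricting the blocks removes the step but not the threshold drift, so the rate should not be read alone.
- Take the best run over blocks 1 to 4 only.
- Report all fifth-block data separately, with feedback and transfer trials distinguished. In sessions 6 to 9 that block still contains feedback trials, and these should not be lost.
- State the number of trials in the added block where the measures are defined.

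The cost is a re-tabulation of data already recorded. The one real downside is that fifth-block data leave the main learning curve. No training rule changes.
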